### Data collection

All data will be collected via two clinic visits lasting 60–90 min, one when the child is 3.5 years, and the other when they are 5 years of age. In brief, the child and parent(s) will have their height, weight and waist circumference measured, and the parent completes the questionnaire while the child undergoes the neuropsychological measures of self-regulation and a hair sample is taken (see below). One week later, parents will be contacted and the accelerometer, remaining questionnaire items, 24-h microbiota food frequency questionnaire, and stool sample will be collected. The dual-energy x-ray absorptiometry (DXA) scan will occur at a separate visit within two weeks of the clinic visit (5 years of age only). Parents will be compensated with a $20 grocery voucher for attending the clinic visit and a $10 grocery for completing the take-home questionnaire. Children will be offered a story book of their choice as a gift. Families who have since left the area but want to continue participating will be able to arrange to have their child (and themselves) weighed and measured at a medical centre, and complete online questionnaires. No other measurements will be obtained for these out-of-town participants.

### Outcome measures

The timing of the outcome measures is presented in Tables 1 and 2. All measures are undertaken by trained research staff blinded to original group allocation.

**Table 1 Tab1:** Outcome measures used to determine the effects of the POI intervention in children at 3.5 years and 5 years of age

				Age	
	Measure	Method	Objectives	3.5 years	5 years
Anthropometry	Height, weight	WHO Growth standards [83]	a	Child	Child
	BMI	Calculated	a	Child	Child
	BMI-for-age z-score	WHO Growth standards [83]	c	Child	Child
	Prevalence of overweight	BMI z-score ≥85th but <95th percentile	c	Child	Child
	Prevalence of obesity	BMI z-score ≥ 95th percentile	c	Child	Child
	Waist circumference	WHO Growth standards [83]	c	Child	Child
Self-regulation	Overall self-regulation	NEuroPSYchological Assessment (NEPSY) [63]	b	Child	Child
		Head-Toes-Shoulders-Knees task [64]	b	Child	Child
		Behavior Assessment System for Children (BASC) [85]	b	Child	Child
		Child Behavior Questionnaire [86]	b	Child	Child
	Sleep-related self-regulation	Researcher generated	b	Child	Child
	Energy self-regulation	Children’s Self-Regulation in Eating scale [87]	b	Child	Child
Body composition	Body fat %	Dual-energy X-ray absorptiometry (DXA) scan	d	-	Child
	Lean mass %	Dual-energy X-ray absorptiometry (DXA) scan	d	-	Child
Sleep	Sleep timing	Accelerometry [104]	e	Child	Child
	Sleep duration	Accelerometry [104]	e	Child	Child
	Awakenings	Accelerometry [104]	e	Child	Child
	Sleep problems	Researcher generated	e	Child	Child
	Sleep hygiene	Researcher generated	e	Child	Child
	Sleep disturbances	Sleep Disturbance Scale for Children [94]	e	-	Child
Physical activity	Physical activity	Accelerometry [72]	f	Child	Child
	Sedentary behaviour	Researcher generated	f	Child	Child
Diet	Dietary pattern scores	Food frequency questionnaire [96]	g	Child	Child
	Nutrient intake	Food frequency questionnaire [95]	g	-	Child

**Table 2 Tab2:** Additional measures collected to determine the predictors of BMI, self-regulation, and sleep consolidation at 3.5 years and 5 years of age

			Child		Parent	
	Measure	Method	3.5 years	5 years	Child age 3.5 years	Child age 5 years
Child gut microbiota	Gut microbiota	From stool sample	Child	Child	-	-
Child mental health	Child depression	BASC-2 [85]	Child	Child	-	-
	Child anxiety	BASC-2 [85]	Child	Child	-	-
	Child stress	Hair cortisol [99]	-	Child	-	-
Parenting practices	Discipline	Researcher generated	-	-	Mother	Mother
Maternal mental health	Maternal depression	Depression, Anxiety and Stress Scale (DASS 21) [100]	-	-	Mother	-
	Maternal anxiety	Depression, Anxiety and Stress Scale (DASS 21) [100]	-	-	Mother	-
	Maternal stress	Depression, Anxiety and Stress Scale (DASS 21) [100]	-	-	Mother	-

#### Anthropometry (objectives a and c)

Trained measurers will conduct all anthropometric measurements following standard protocols [82]. Weight will be obtained with children wearing standard clothing (singlet and underwear) using regularly calibrated electronic scales (Tanita WB-100 MA/WB −110 MA). Height will be measured using a Harpenden stadiometer (Holtain Ltd, UK). Waist circumference will be measured at the minimum circumference between the rib cage and the iliac crest using a Rosscraft Anthropometric tape (Rosscraft Innovations Inc, USA). A third measurement will be made if duplicate measures are not within 0.1 kg for weight, 0.7 cm for height, and 1.0 cm for waist circumference (with the mean of the two closest measurements used in such cases) [38]. Weight-for-age z-score and BMI-for-age z-scores will be calculated using the WHO growth standards [83], with overweight defined as a BMI-for-age z-score ≥85th to <95th percentile and obesity defined as ≥95th percentile.

#### Self-regulation (objective b)

*Overall self-regulation* will be determined using the laboratory-based measures NeuroPSYchological Asssessment (NEPSY-2) [63] and the Head-Toes-Knees-Shoulders task [64]. The NEPSY-2 is a test battery assessing numerous areas of neuropsychological functioning. It is well-normed, reliable, and appropriate for use with 3–5 year-old children. Five subtests from this battery will be used in this study to assess targeted areas of neuropsychological functioning: ‘Statue’ which measures inhibitory control, ‘Comprehension of Instructions’ which assesses working memory, ‘Visuomotor Precision’ which measures inhibition and fine motor control, and ‘Phonological Processing’ and ‘Word Generation’ which both assess language development. In addition, children will complete the Head-Toes-Knees-Shoulders task, a measure of behavioural regulation and inhibition [64, 84]. As well as these laboratory measures, self-regulation will also be assessed using parent-report questionnaires to assess children’s day-to-day abilities to self-regulate behaviour outside the setting of the study assessment session. These questionnaires include the Behavioral Assessment System for children (BASC-2) [85] and the Children’s Behavior Questionnaire (CBQ) [86]. The BASC-2 is a well-validated and normed scale designed to assess wide-ranging areas of child functioning, as rated by parents and/or teachers. At both ages four subsets of the BASC will be assessed, namely ‘Hyperactivity’, ‘Attention Problems’, ‘Emotional Self-Control’, and ‘Executive Functioning’. The CBQ is an extensively used and validated measure of child temperament and items load into 3 broad factors: ‘Surgency’ which is a measure of positive affect and approach, ‘Negative Affect’ which indicates sensitivity to frustration and punishment, and ‘Effortful Control’ which evaluates attentional self-regulation. The latter two factors will be used as indicators of self-regulatory abilities.

*Sleep-related self-regulation* will be assessed using brief questions asking parents how often (six-point likert scale) their child falls asleep on their own, requires a parent to hold them or be in the room in order to fall asleep, has difficulty falling asleep, and stays in their own bed all night.

*Energy self-regulation* will be assessed using a brief eight-item questionnaire [87], which asks parents to agree or disagree (five-point likert scale) with eight statements covering issues such as the child knowing when they are full, eating when they are already full, and not eating snacks if they are already full.

#### Body composition (objective d)

Body composition will be assessed by dual-energy x-ray absorptiometry (DXA) at 5 years of age only. All DXA measurements will be performed and analysed by one experienced operator with a Lunar Prodigy scanner (software package 16.0; Lunar, Madison, WI) using standard procedures. The scanner determines total fat mass (kg) and the fat content (kg) of specific anatomical regions including trunk and extremity fat (automatic default regions) and central and peripheral fat (manual regions of interest) [88, 89]. In our laboratory the CVs for repeated in vivo scans on ten adults were 1.8 % for fat mass, 1.8 % for fat percentage, and <2.5 % for all regional measurements. The scans are well tolerated by children at this age (>95 % usable scans).

#### Sleep, physical activity and sedentary behaviour (objectives e and f)

Measures of habitual physical activity (counts per minute, time spent at different intensities of activity) and 24 h-sleep patterns (sleep-wake timing, sleep duration, night awakenings, overnight sleep efficiency, daytime naps) will be measured by five consecutive days of accelerometer recording including at least one weekend day (Acticals, Mini-Mitter, Bend, OR) [49] in all children. The accelerometer will be fitted to the child during the clinic visit. Children will be asked to wear the accelerometer 24 h a day for the full 5 days. The accelerometers are initialised using 15 s epochs and a valid day is defined as at least 8 h of wear time. Data will be cleaned and scored using an automated script developed in MATLAB (MathWorks, Natick, MA, USA). The program is initiated using a “time flag” for sleep onset and for sleep offset, approximately half an hour before the average bedtime and wake times for this age group. To detect sleep and wake states the count-scaled algorithm [90] is activated to detect wake “events” as the last of 15 continuous minutes of sleep followed by 5 min of awake and sleep “events” as the start of 15 continuous minutes of sleep preceded by 5 min of awake. Nap screening rules will be applied to the data for the 3.5 year olds to identify naps as sleep periods that occurred during the period of 9 am to 5 pm, where a sleep period is defined as at least 20 min of sleep, preceded by 5 min of awake and using a minimum sleep time threshold of 30 min [91]. Non-wear time applies to the period of time between sleep offset (morning wake) and bedtime and is defined as 20 min of consecutive zeros. Standard sleep-wake variables including nap counts and timing will be calculated using the automated script within MATLAB. Subjective measures of sleep will be collected by questionnaire. Data will be analysed for physical activity during waking hours only and expressed as both counts/min (measured in 15 s epochs) and in terms of intensity of activity (sedentary, light, moderate, vigorous) using the cutoffs of Evenson et al. [92] as recently recommended [93].

Data on parents’ perceptions of their child’s sleep as problematic, sleep hygiene covering the pre-sleep routine (for example bathing, reading, quiet time, use of electronic media), the sleep environment (who the child sleeps with, bedding and lighting arrangements), and sleep disturbances (snoring, restless legs, sleepwalking, nightmares and night terrors) will be collected by questionnaire. Parents will also complete the Sleep Disturbance Scale for Children when their child is 5 years of age [94]. Information on children’s electronic media use will also be collected from all children via questionnaire. This will include: the variety of media in the house (television, DVD, computer, tablet, cellphone, ‘iPod’), usual time spent on each device by the child, family rules around viewing, and viewing situations such as who the child was with, and where the device was viewed [38].

#### Diet (objective g)

In order to minimise respondent burden and thus achieve higher rates of participant retention, dietary intake (food pattern scores and nutrient intake) will be assessed using an interviewer administered food frequency questionnaire (FFQ) rather than diet records or 24-h recalls. At both 3.5 and 5 years of age, the FFQ will be based on the EAT FFQ that has been validated for measuring both nutrient intake [95] and dietary patterns [96] in young children. At 3.5 years, the FFQ will collect data on the frequency (13 frequency categories: ‘not eaten this month’ to ‘five or more times a day’) with which 90 food items have been consumed over the past month. At 5 years of age, the EAT5 FFQ will collect data on amount eaten as well as frequency of intake over the past month (ten frequency categories: ‘not eaten this month’ to number of times a day). Amounts will be collected as number of specified units (e.g. 1 biscuit), or volume (e.g. ml of rice) with the parent using dried beans or rice to demonstrate a typical portion size for that food. The 113 foods in the EAT5 FFQ will include foods from the original EAT FFQ that are still relevant at 5 years of age (i.e. excluding infant foods) with additional foods that are rich sources of food components that may influence the gut microbiota (i.e. resistant starch, polyphenols, choline). In addition, at 5 years of age the parent will be asked to complete a self-administered recall when they collect their child’s faecal sample (see next section). This recall will refer to the day before the sample was collected and is the same as the EAT5 FFQ but asks for frequency of intake only, not amount eaten.

#### Additional measures

##### Gut microbiota

A small stool sample (approximately 5 g) will be collected from each participant at 3.5 and 5 years. The sample will be placed into a specially provided freezer flask and stored in the home freezer before retrieval by POI research staff following notification of sample collection. The sample will be stored at −80 °C for later analysis of the composition of the stool microbiota. These analyses will focus on bacterial community phylogenetics using high throughput sequencing of amplicons generated from the 16S rRNA gene. DNA will be extracted from stool using the MoBio PowerSoil DNA Isolation kit according to the Human Microbiome Project standard operating procedures (http://www.hmpdacc.org/tools_protocols/tools_protocols.php). Genomic DNA will be submitted to Argonne National Laboratories for barcoded amplification of the V4 region of the bacterial 16S rRNA gene and sequencing on a MiSeq (Illumina) instrument. DNA sequences will be processed using the QIIME v. 1.9.1 suite of programs [97]. Genus level taxonomy will be obtained by filtering Operational Taxonomic Unit (OTU) tables containing taxonomic data generated using the RDP classifier, at a genus level, extracting representative sequences and using BLAST to identify genus level matches within the NCBI database. Alpha- and beta-diversity analysis of phylogenetic data will compare the coverage and richness (number of phylotypes), and similarity or difference in the composition of the stool microbiota between subject groups. Finally, the proportions of the major bacterial families and genera comprising the stool microbiota will be compared between normal and overweight children.

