The key objectives are to determine whether the POI ‘Sleep intervention’ or ‘FAB intervention’ from late pregnancy to 2 years of age result in differences in:BMI z-score at 3.5 and 5 years of age (primary objective)Self-regulation (overall, sleep-related, or energy) at 3.5 and 5 years of ageOther weight indices (BMI, prevalence of overweight or obesity, waist circumference) at 3.5 and 5 years of ageBody composition at 5 years of ageSleep (timing, duration, awakenings, problems) at 3.5 and 5 years of agePhysical activity at 3.5 and 5 years of ageDiet at 3.5 and 5 years of age.

Additional objectives include determining, in a cohort analysis, possible predictors of BMI, self-regulation (overall, sleep-related, energy), and sleep consolidation (timing, duration, awakenings, problems) at 3.5 and 5 years of age.

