### Sample size

Retention at 2 years was 86 % (*n* = 686/802) which is higher than was anticipated in our original power calculations (20 % loss to follow-up was assumed) [38]. Based on this, we anticipate retaining at least 75 % of the original cohort through to age five, giving us an estimated sample size at 5 years of at least 600 participants. This would provide 80 % power to detect a difference in BMI of 0.3 kg/m^2^ or larger at 5 years of age between any pair of the four groups using a two-sided test at the 0.05 level, based on earlier data from this research group suggesting a standard deviation of 0.8 [49]. This sample size would also allow 80 % power for detecting differences in self-regulation scores of 0.35 standard deviations between any two arms of the trial (falling between a “small” and “moderate” effect size) and detecting correlations at the study level of 0.12 or larger between continuous measures (e.g. between parenting style at 12 months and self-regulation at 5 years and between consolidated sleep hours at 6 months, and self-regulation at 3.5 and 5 years) using two-sided tests at the 0.05 level.

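### The one taxon-level contrast named for the stool microbiota splits BMI into normal versus overweight, and the plan does not say that the more efficient analysis on continuous BMI z-score takes precedence

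*Protocol article*

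**What the plan says.** The Gut microbiota section (under Additional measures) closes by stating that "the proportions of the major bacterial families and genera comprising the stool microbiota will be compared between normal and overweight children". The sentence before it describes alpha- and beta-diversity analyses of "similarity or difference in the composition of the stool microbiota between subject groups", without saying which groups are meant.

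Four other places bear on this:

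- The end of the Background gives the purpose of the cohort work: "Additional objectives include determining, in a cohort analysis, possible predictors of BMI, self-regulation (overall, sleep-related, energy), and sleep consolidation". By its title, Table 2 holds the measures collected for that purpose, and gut microbiota is its first entry.
- The Sample size section supports the cohort work by power for "detecting correlations at the study level of 0.12 or larger between continuous measures".
- The Anthropometry section provides a BMI-for-age z-score from measured height and weight. It defines overweight as the band from the 85th to below the 95th percentile, with obesity a separate class from the 95th upward.
- The Analysis section specifies linear models for continuous outcomes in the key objectives, and models of a similar kind for the additional objectives.

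**The concern.** The objective names BMI, and the power statement is for pairs of continuous measures, yet the specific sentence on taxa compares two BMI categories. No reason for the split is given there. A child just above the 85th percentile is then treated as wholly different from one just below it, and BMI variation within each category is ignored. The result would describe category membership rather than BMI.

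At stake is sensitivity to modest associations. The Background criticises earlier microbiota studies for small numbers and parent-reported BMI. Cutting a well-measured BMI in two gives back part of the advantage that this cohort has over them. A team that followed the Gut microbiota section literally would report the two-group result.

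**Working it through.** **Inputs.** From the Sample size section: n = 600 ("giving us an estimated sample size at 5 years of at least 600 participants"; 0.75 × 802 = 601.5), r = 0.12, 80% power and two-sided α = 0.05. From the Background: national figures at 2–4 years of 9.5% obese and a further 20% overweight, so 9.5 + 20 = 29.5% at or above the overweight cut.

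**Assumptions.** The documents give no microbiota effect size, no power for this comparison and no overweight prevalence for this cohort. So r = 0.12 and 29.5% are borrowed, and both are varied below. BMI z-score and suitably transformed taxon abundance are taken as bivariate normal with a linear relation.

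**Step 1: the plan's own figure.** Power = Φ(atanh(r)·√(n − 3) − 1.960). With r = 0.12 and n = 600: 0.1206 × 24.43 = 2.946; 2.946 − 1.960 = 0.986; power = 83.8%. The stated 80% is therefore slightly conservative: 543 children would suffice for r = 0.12, and the smallest correlation detectable with 80% power at n = 600 is 0.114.

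**Step 2: the cut.** Splitting a normal variable with a fraction p above c = z(1 − p) multiplies the correlation by φ(c)/√(p(1 − p)). The information kept is the square of that factor. At p = 0.295 the factor is 0.757, so r becomes 0.757 × 0.12 = 0.091. The information kept is 0.572, a loss of 43%, equivalent to analysing about 343 of the 600 children. Power = Φ(0.0910 × 24.43 − 1.960) = 60.4%, a loss of 23.4 points. A simulation of 20,000 data sets gave 83.8% and 60.4%.

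**Step 3: vary the share above the cut** (n = 600, r = 0.12, continuous power 83.8%).

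| Share above cut | Information lost | Power after cut | Points lost |
|---|---|---|---|
| 50% | 36% | 65.0% | 18.8 |
| 35% | 40% | 62.7% | 21.1 |
| 29.5% | 43% | 60.4% | 23.4 |
| 20% | 51% | 53.9% | 29.9 |
| 15% | 57% | 48.3% | 35.5 |

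The 15% row is the reference-population share at or above the 85th percentile. The 50% row is the most favourable cut in this setting.

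**Step 4: vary the correlation** (29.5% above the cut, n = 600). The loss is 18.4 points at r = 0.08 (50.0% to 31.6%), 16.3 at r = 0.15 (95.8% to 79.5%) and 3.7 at r = 0.20, where both powers are above 95%.

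**Step 5: fewer samples.** The Data collection section says that out-of-town families give no measurements beyond height, weight and online questionnaires, so the number with stool samples will be below the number followed up. For illustration, n = 400 with r = 0.12 and 29.5% above the cut gives 67% against 44%.

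**Step 6: the meaning of overweight.** Steps 2 to 5 pool obese with overweight children. If the Anthropometry definition is taken literally and obese children are left out, 70.5% (423 children) are compared with 20% (120 children). On the z-score scale the group means are −0.489 and 0.880, so the expected difference is 0.12 × 1.369 = 0.164, with standard error √(1/423 + 1/120) = 0.103. Power is about 35.5%, and about 71% of the information is lost. The text does not say which reading applies.

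**The case against.** The strongest reply is that a continuous analysis is already provided for. Table 2 places gut microbiota among the predictor measures, the objective names BMI, and the Analysis section extends its regression models, linear for continuous outcomes, to the additional objectives. The Gut microbiota section is mainly about collection and sequencing, and never claims that its closing comparison is the only or the main analysis. This stands. A reader might infer that the study throws away continuous BMI altogether, but the documents do not support that. What remains is that the general provision does not mention taxa or say which analysis leads, while the specific sentence names only the split.

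A reader might also take the diversity sentence as further cutting of BMI. The documents do not support that either: the subject groups are undefined and may be the trial arms, for which a group comparison is right.

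The group contrast also has a scientific setting. The Background cites work on lean and obese mice and on later overweight status, and overweight prevalence is a listed outcome. That justifies keeping the contrast for comparison with other work, but not letting it lead.

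Finally, the inputs are borrowed. The examples given for r = 0.12 are parenting style or sleep against self-regulation, the prevalence is national, and 600 is not the number of stool samples. This too stands, so no single figure can be given as the loss.

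**Conclusion.** The point holds in a limited form. The specific text on taxa names only a categorised comparison, which is less efficient than continuous BMI z-score and does not match the predictors-of-BMI objective. The Analysis section permits the better analysis without giving it precedence.

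The size is conditional. The loss of 43% of the information and 23 points of power is one scenario, and reading it as an established loss for this study would go beyond the documents. The ranges in the working rest on normality and linearity, which the documents do not establish for taxon abundance. Within that setting no cut loses less than 36% of the information, though for stronger associations the effect on power is small.

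Gut microbiota is an additional measure outside the key objectives, so no primary or key conclusion is affected. The change is still worth making because it costs almost nothing.

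**What to change.** In the Gut microbiota section, make models with continuous BMI-for-age z-score the main analysis of the association between taxa and BMI, consistent with the Analysis section, with suitably transformed family and genus abundance and a check for non-linearity such as a spline term. Keep the normal-versus-overweight comparison as a descriptive display, and state whether overweight there includes obese children, given the Anthropometry definition. Say what the subject groups in the diversity sentence are. Apply the same change to diversity only where they are BMI groups; comparisons of trial arms stay as they are.

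The cost is a few words of analysis text and no new data. The small downside is that a slope is slightly harder to present than two groups, and its linearity has to be checked.
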